#### Secondary outcomes

For binary outcomes, risk ratios and 95% CIs will be estimated, following the same planned analysis as for the severe respiratory failure outcome. For normally distributed continuous outcomes, mean or median differences with 95% CIs will be calculated using linear regression. If the data show significant skewness, median differences with 95% CIs will be calculated using quantile regression. As per the primary outcomes, both crude and adjusted estimates will be presented, but the primary inference will be based on estimates adjusted for minimisation factors.

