### Intervention description {11a}

The investigational medicinal product (IMP) is CUROSURF^®^, a natural animal-derived surfactant manufactured and supplied by Chiesi Farmaceutici S.p.A. at [name]. The Reference Safety Information (RSI) will be the latest approved Summary of Product Characteristics (SmPC) for the surfactant used.

The recommended starting dose for the IMP is 100–200 mg/kg (1.25–2.5 ml/kg), administered in a single dose as soon as possible after diagnosing respiratory distress. The administration of the IMP will be as per local site policy and procedure and may be completed by any clinician for whom this falls within their usual scope of practice, following confirmation of eligibility by a doctor or advanced neonatal nurse practitioner. As part of the intervention in this trial, surfactant will be given to infants as soon as possible after randomisation.

The IMP is a commonly used drug in NNUs and is being used in line with standard care. Side effects are uncommon and usually transient during administration.

The timing and dosage of IMP administration will be collected. Surfactant is a stock drug for all NNUs and will be administered and accounted for as per local practice. No specific contraindications are known.

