### Outcomes {12}

The primary and secondary outcome measures are detailed in Table 2.

**Table 2 Tab2:** Primary and secondary outcome measures

**Outcome measures**	**Time point(s) of evaluation of this outcome measure**
•*Length of infant’s hospital stay* after birth, defined as the number of days from birth to discharge home from hospital	Between birth and discharge home from hospital
•*Incidence of severe respiratory failure*, defined as sustained (≥ 30 min) requirement for *FiO*_*2*_ ≥ 0.45 to maintain oxygen saturations (SaO_2_) ≥ 92%	Between trial entry and discharge home from hospital
**Perinatal clinical outcome measures**	**Time point(s) of evaluation of this outcome measure**
•*Total duration of NNU stay*, defined as total number of days of inpatient care in a neonatal unit (defined according to Healthcare Resource Group (HRG) Critical Care categories 1–5, 2016)	Between trial entry and infant discharge home from hospital
•*Total duration of neonatal intensive care*, defined as number of days of neonatal intensive care (defined according to HRG Critical Care categories 1–5, 2016)	
•*Duration of mechanical ventilation*, defined as days of ventilation via an ETT (endotracheal tube)	
•*Duration of noninvasive respiratory support*, using positive airway pressure or high flow	
•*Pulmonary air leaks*, requiring insertion of a chest drain	
•*Days of mother-infant separation*, defined using HRG Critical Care categories 1–5, 2016	
•*Breast milk feeding*, defined as (a) any breast milk feeding during neonatal hospital stay, (b) any breast milk feeding at hospital discharge, and (c) exclusive breast milk feeding at hospital discharge	
•*Late onset sepsis*, defined as the incidence of *microbiologically confirmed or clinically suspected* invasive infection more than 72 h after birth	
•*Need for inhaled nitric oxide (iNO) therapy*	
•*Need for extracorporeal membrane oxygenation (ECMO)*	
•*Medical respiratory diagnoses*, defined as any respiratory diagnosis attributed to the infant	
•*Surfactant administration*, defined as (a) administration of any additional surfactant in infants randomised to receive early surfactant or (b) administration of any surfactant in infants receiving expectant management, including number of doses and dose given	
•*Maternal length of hospitalisation*, defined as the total number of days spent by the mother in hospital after trial entry	Between trial entry and maternal discharge home from hospital

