### Sample size {14}

One of the primary outcomes is the length of hospital stay from trial entry to discharge home. Reported length of stay for late preterm infants with respiratory distress is estimated to be between 10 and 15 days from the literature [4, 10, 18]. Calculations are based on the reduction in median length of stay in NNU from 12 to 10 days in the early surfactant versus expectant management group. To detect a 2-day reduction in the length of stay (equivalent to a hazard ratio of 1.2) with 90% power and a two-sided 5% significance level, a total sample size of 1280 is required. We estimate the prevalence of multiple births in our patient population to be 25% [19] with an intra-class correlation coefficient of 0.9, based on previous perinatal trials. Allowing for an inflation factor of 1.13 for this and a 5% attrition rate, the required recruitment target is 1522 (761 per group). Based on data from NNUs, around 40–50 late preterm and early term infants per year require respiratory support. We aim to recruit an average of two infants per month over 30 months in approximately 45 NNUs to reach the target sample size of 1522, allowing for a staggered start.

The other primary outcome is the proportion of infants who reach a predefined higher threshold of disease severity, at which clinicians may choose to give ‘rescue’ surfactant. A recent study [20] reported an event rate of 45% in a cohort of late preterm infants admitted to neonatal intensive care for respiratory failure. This is likely to be lower in the trial population, which also includes early term infants. With a sample size of 1522, a treatment difference of 9% could be detected with 90% power and a two-sided 5% significance level if the expectant management group event rate was 45%. A smaller treatment difference could be detected if the expectant management group event rate (CER) was lower than this (e.g. 8% difference for a CER of 35%, 7% difference for a CER of 25%).

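### The skewness rule sends days of mechanical ventilation to a median difference, which will be 0 and uninformative if, as is likely, fewer than half of each arm is ventilated

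*Protocol article*

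**What the plan says.** The paragraph on secondary outcomes in the protocol article gives two branches for continuous variables. The first is "For normally distributed continuous outcomes, mean or median differences with 95% CIs will be calculated using linear regression". The second is "If the data show significant skewness, median differences with 95% CIs will be calculated using quantile regression". No outcome is exempted, and skewness has no stated criterion. Crude and adjusted estimates are both to be shown, but "the primary inference will be based on estimates adjusted for minimisation factors".

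Table 2, under Outcomes {12}, includes duration of mechanical ventilation, "defined as days of ventilation via an ETT (endotracheal tube"). It lists no yes/no outcome for any ventilation. Under Eligibility criteria {10}, infants enter after a decision to give noninvasive support, and earlier intubation is an exclusion.

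No ventilation rate appears anywhere. The nearest figure is in Sample size {14}, for the threshold of severe respiratory failure: a published study "reported an event rate of 45% in a cohort of late preterm infants admitted to neonatal intensive care for respiratory failure", to which the authors add "This is likely to be lower in the trial population, which also includes early term infants". Their worked examples for the expectant arm are 45%, 35% and 25%.

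**The concern.** A duration that is zero for most infants and positive for the rest is right-skewed, so the rule selects the median. When more than half of the values in each arm are zero, both medians are zero and their difference carries no information about how many infants were ventilated or for how long.

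This matters more than usual for a secondary outcome, for three reasons. The rationale for the early surfactant group is that it should reduce the need for invasive support and ventilation. Because Table 2 records ventilation only as a duration, no planned binary analysis would recover the effect. And the section on primary outcomes says that discordant primary results will be read in the light of the secondary outcomes. A median difference of 0 could then be taken as lack of corroboration when it is a property of the summary measure.

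**Working it through.** **Reproducing the plan's own figure.** The document gives no figure for ventilation, so only the sample size can be reproduced. For a hazard ratio of 1.2, 90% power and two-sided 5%, the Schoenfeld formula gives 1265 and the Freedman formula 1272, against 1280 stated. Then 1280 × 1.13 / 0.95 = 1522.5, against 1522 stated. The checks below use 1280 / 2 = 640 infants per arm.

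**When the median is zero.** Let p be the share of an arm with any ventilation days. The arm's sample median is 0 whenever fewer than half of its infants are ventilated. With n = 640 and independent infants, the number ventilated has mean 640p and variance 640p(1 − p). The distance from the 50% mark in standard deviations is z = (320 − 640p) / √(640p(1 − p)).

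- p = 0.40: z = (320 − 256) / √153.6 = 64 / 12.39 = 5.2. A non-zero median is practically impossible.
- p = 0.45: z = (320 − 288) / √158.4 = 32 / 12.59 = 2.5. A non-zero median has a chance of about 0.6%.

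So for any p up to about 45% in both arms, the crude difference is almost certain to be 0, whatever the gap between the arms.

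**Simulation of the rule.** Ventilated shares and durations are assumptions, since the documents give none. Days are zero if not ventilated, and otherwise exponential and rounded up. There were 60 runs per scenario. The adjusted model is median regression on arm, gestation week and multiple birth; centre was left out.

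| Ventilated, expectant vs early | Difference in mean days | Crude median difference | Adjusted median difference |
|---|---|---|---|
| 10% vs 5% | −0.19 | 0 in every run | 0 in every run |
| 20% vs 10% | −0.36 | 0 in every run | 0 in every run |
| 30% vs 15% | −0.98 | 0 in every run | 0 in every run |
| 45% vs 20% | −1.51 | 0 in every run | 0 in every run |
| 45% vs 36% | −0.75 | non-zero in 1 of 60 | 0 in every run |
| 20% vs 60% | +0.22 | +1 | +1 |
| 60% vs 40% | −0.71 | −1 | about −1 |

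A second set, with 2000 trials per scenario and gamma-distributed days (shape 2, scale 1.5, rounded up, averaging about 3.5 days if ventilated), gave a crude median difference of 0 in all trials at 30% vs 20% and at 40% vs 25%. The mean differences were −0.35 and −0.52 days, which agree with 0.10 × 3.5 = 0.35 and 0.15 × 3.5 = 0.525.

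**The interval.** Bootstrapping the crude median difference under those two scenarios gave a 95% interval of zero width, from 0 to 0. That is not precision: it means only that no resample crossed 50%.

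**Above 50%.** The last two rows of the table show the other failure. At 20% vs 60%, with short episodes in the early arm, the median difference is +1 day while the mean difference is +0.22, so the median overstates it more than fourfold (1 / 0.224 = 4.5).

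**The case against.** The strongest objection concerns the premise. The 45%, 35% and 25% are expectant-arm rates of an oxygen requirement, not ventilation rates, and they do not bound ventilation: in either group an infant may be intubated for another reason. Nor is the route of dosing fixed, since "The administration of the IMP will be as per local site policy and procedure". If tube ventilation around dosing is counted, most of the early arm could have non-zero days. This stands. A reader might infer that the rule returns zero whatever the treatment does, but the documents do not support that, and the 20% vs 60% scenario contradicts it. A zero majority in both arms is likely, not established. The objection does not rescue the rule, because above 50% the estimate becomes a jump of a day or more.

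A reader might also extend the point to days of neonatal intensive care, "defined as number of days of neonatal intensive care". No figure in the document says how many infants will have none, so this is a matter to check and not part of the finding. Nor is the switch between mean and median a main charge: for ventilation days the branch is predictable in advance.

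Two mitigations are fair. The economic evaluation reports its main outcomes as means and mean differences, but does not name ventilation days among them. The SAP, not shown here, is to give the detailed methods and may treat such outcomes separately. But the point concerns a rule that the article states without exception, not a detail that it omits. Severe respiratory failure, air leaks, nitric oxide and ECMO also inform severity, so interpretation does not rest on ventilation days alone.

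**Conclusion.** The concern holds in limited form. For duration of mechanical ventilation, the stated rule gives a median difference of 0 with an uninformative interval as long as fewer than half of each arm is ventilated. In the scenarios examined it hid reductions of 0.19 to 1.51 mean days per infant. If either arm exceeds half, the estimate moves by about a day and reflects mainly that crossing.

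The conclusion rests on one judgement, that most infants in both arms will have no ventilation days. The entry criteria make this likely and no stated rate confirms it. The day counts rest on assumed shares and durations; the zero result does not, provided both shares stay clearly below 50%. The rule remains suitable for durations that nearly all infants have, such as neonatal unit stay. The primary analyses are unaffected. This should be changed, but it does not threaten the trial.

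**What to change.** For ventilation days, replace the median difference with two fixed quantities:

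1. The proportion of infants with any ventilation days, as a risk ratio and risk difference by the binary method already planned.
2. The difference in mean days over all randomised infants, adjusted for the minimisation factors, with a confidence interval that allows for clustering of multiples, for example a bootstrap that resamples pregnancies.

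Apply the same pair to any other duration that is zero in about half or more of the infants, judged on data pooled across arms and before any comparison by arm. The pooled check matters because the trial statisticians are not fully blinded. Keep median regression for durations that are positive in nearly all infants, and name them. State whether ventilation given only around dosing counts, and how deaths enter the mean. If the SAP already does this, the article's rule needs only a matching exception.

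The cost is analysis wording and modest programming, with no new data. The drawback is that a mean is sensitive to a few long episodes, which is why the proportion should be reported beside it.

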### Interim analyses {21b}

A Data Monitoring Committee (DMC), independent of the applicants and Trial Steering Committee (TSC), will review the progress and accumulating data from the trial at least annually and provide advice on the conduct of the trial to the TSC. DMC meetings will include open and closed sessions. The open session will cover recruitment, data quality, and pooled safety data. The closed session will focus on accumulating efficacy and safety data by trial arm. Outcomes will be reported with summary statistics, but treatment effects, *p*-values, and confidence intervals will be excluded unless requested by the DMC.

If appropriate, the DMC may recommend early stopping due, for example, to clear benefit or harm of a treatment or external evidence, e.g. published results of another trial. The TSC will review these recommendations and act upon them. If deemed appropriate, the TSC will carry the responsibility for deciding if the trial should stop recruitment early.

### Methods for additional analyses {20b}

#### Subgroup analyses

Pre-specified subgroup analyses will be conducted to examine the consistency of the effect of the intervention across gestational age groups (late preterm vs. early term) and first type of noninvasive respiratory support given (high flow vs. positive airway pressure) using the statistical test of interaction. 95% confidence intervals with a two-sided 5% level of significance for statistical inference will be presented.

No sensitivity analyses have been specified.

### Methods in analysis to handle protocol nonadherence and any statistical methods to handle missing data {20c}

Adherence to trial intervention will be reported by trial arm. Missing data will be described, for example, by presenting the number of individuals in the missing category. Missing data as a result of babies being lost to follow-up is expected to be minimal for short-term outcomes. No imputation of missing data is planned.

A restricted secondary analysis on the two primary outcomes will be performed, excluding infants who received surfactant outside of surfactant administered according to allocation without meeting the criteria for the severe disease threshold.

#### Economic evaluation

An economic evaluation will be conducted alongside the main clinical analysis. The statistical analysis of the economic evaluation will be conducted according to a pre-specified health economics analysis plan (HEAP), which will be available in a separate document. Therefore, only a brief account of health economic analysis is included in this protocol.

The primary objective of the health economic evaluation will be to calculate the 12-month cost-effectiveness of early surfactant therapy versus expectant management in a within-trial economic evaluation. This analysis will take the form of a cost-consequence analysis of key clinical primary and secondary outcomes alongside maternal quality of life, mother’s health care costs up to hospital discharge, and infant health care costs at 12-month follow-up.

A UK NHS perspective only including direct healthcare costs will be adopted for the analysis. Resource use will be collected for two different time periods: up to initial hospital discharge and from hospital discharge to 12-month follow-up. Initial hospital resource use will be collected both for babies and mothers (length of stay only). For infants, we will collect data on the inpatient days of high-, medium-, and low-level care needed after delivery and transfers out of the hospital. After initial hospital discharge, information on infants’ use of inpatient hospital stays, critical care whilst admitted, visits to accident and emergency (A&E) department, and hospital outpatient consultations will be collected up to the 12-month follow-up. All resource use will be valued in monetary terms using appropriate UK unit costs relevant to the time of analysis.

Maternal quality-adjusted life-years (QALYs) will be derived from utility scores obtained using the EQ-5D-5L quality-of-life instrument [21, 22]. For the cost-consequence analysis maternal QALYs, maternal health-related quality-of-life (HRQoL) domains and values from the EQ-5D-5L quality-of-life instrument will also be reported alongside the trial’s primary endpoints and selected key secondary outcomes. Measurements of maternal HRQoL using the EQ-5D-5L data will take place at baseline, initial hospital discharge, and 12-month follow-up.

The different components (costs and consequences) of the cost-consequence analysis will be presented in a disaggregated and tabulated manner and presented separately up to hospital discharge and at 1-year follow-up. Main outcomes for the cost-consequence analysis will be presented as mean estimates with associated 95% CIs for each group in the trial. Mean differences and associated 95% CIs between the two arms of the trial will be estimated using common statistical models including ordinary least squares or generalised linear models (GLM) regression analysis to adjust (if necessary) for potential imbalances at baseline.

### Plans to give access to the full protocol, participant level-data and statistical code {31c}

Prior to the recruitment of the first participant, the trial will have been registered on a publicly accessible database. The trial information will be kept up to date during the trial, and the chief investigator or their delegate will upload results to all those public registries within 12 months of the end of the trial declaration. All data requests should be submitted to the corresponding author of the main results paper for consideration. Access to de-identified patient data may be granted for secondary analysis following review. If approved, a data sharing agreement will be put in place. Data availability will begin with the publication of the final results.

## Oversight and monitoring

### Composition of the coordinating centre and trial steering committee {5d}

The trial will be overseen by a TSC, DMC, and a Project Management Group (PMG).

The Project Management Group, consisting of the CI and members of the NPEU Clinical Trials Unit, will conduct central monitoring to ensure the trial is conducted according to the protocol. The PMG will meet every 3 to 4 weeks. Central monitoring will include reviewing recruitment rates, data quality, and safety events.

The TSC will consist of independent members, including a chair, clinicians, statisticians, and patient and public involvement representatives. The TSC will meet at least annually to review the trial’s progress, provide scientific advice, and make decisions regarding the trial’s continuation or termination. The TSC will oversee the trial’s conduct, monitor safety and efficacy, and act upon recommendations from the DMC.

### Composition of the data monitoring committee and its role and reporting structure {21a}

The DMC will consist of independent members, including a chair, clinician, and statistician, who are separate from the trial team and TSC. During recruitment, the DMC will meet annually or more frequently as needed to review trial conduct, progress, and accumulating data. The DMC will then make recommendations to the TSC. The DMC Charter, outlining roles, responsibilities, and conduct, will be established at the initial meeting.

### Adverse event reporting and harms {22}

The safety reporting window for this trial will be from randomisation to infant’s discharge home.

An independent DMC will review study data, including serious adverse events (SAEs). The DMC is responsible for safeguarding participants’ well-being and will make recommendations to the TSC regarding trial continuation or protocol modifications. The TSC ultimately decides whether to terminate the trial for safety reasons.

On-site medical staff assess the relationship between adverse events (AE) and the trial supplement. However, due to the inherent characteristics of the patient population, determining causality can be challenging. Therefore, only unforeseeable serious adverse events will be documented under the trial’s safety reporting procedures.

Suspected unexpected serious adverse reactions (SUSARs) must be reported to the MHRA (Medicines & Healthcare Products Regulatory Agency) and the approving REC within 7 days if the event results in death or is life-threatening and within 15 days for all other SUSARs. Additionally, a copy of the SAE form related to the event will be forwarded to the Chair of the DMC for review.

Events of particular interest (which must also be reported as SAEs) are as follows:

DeathTransfer to another hospital related to early respiratory management◦For escalation of care◦For neonatal intensive care because of lack of intensive care cot capacity in the NICU or LNU of birth (NB, transfers for a lower level of care (SCU) or for reasons unrelated to respiratory management do not need to be reported as an SAE)Serious complication of ETT intubation such as hypoxia resulting in encephalopathySevere pulmonary haemorrhageSevere intracranial haemorrhage

The full protocol provided to sites specifies foreseeable SAEs within the trial population that do not require reporting.

